# Efficacy of ganglion impar block combined with pudendal nerve pulsed radiofrequency for pudendal neuralgia management—a randomized clinical trial

**DOI:** 10.1186/s13063-024-08152-3

**Published:** 2024-05-13

**Keywords:** Ganglion impar block, Pudendal neuralgia, Pudendal nerve block, Pulsed radiofrequency

## Abstract

**Background:**

Pudendal neuralgia is a chronic and debilitating condition. Its prevalence ranges from 5 to 26%. Currently, therapeutic approaches to treat pudendal neuralgia include patient education, medication management, psychological and physical therapy, and procedural interventions, such as nerve block, trigger point injections, and surgery. Drug therapy has a limited effect on pain relief. A pudendal nerve block may cause a significant decrease in pain scores for a short time; however, its efficacy significantly decreases over time. In contrast, pudendal nerve pulsed radiofrequency can provide pain relief for 3 months, and ganglion impar block has been widely used for treating chronic perineal pain and chronic coccygodynia. This study aimed to determine the efficacy and safety of monotherapy (pudendal nerve pulsed radiofrequency) and combination therapy (pudendal nerve pulsed radiofrequency plus ganglion impar block) in patients with pudendal neuralgia.

**Methods:**

This randomized, controlled clinical trial will include 84 patients with pudendal neuralgia who failed to respond to drug or physical therapy. Patients will be randomly assigned into one of the two groups: mono or combined treatment groups. The primary outcome will be a change in pain intensity measured using the visual analog scale. The secondary outcomes will include a Self-Rating Anxiety Scale score, Self-Rating Depression Scale score, the use of oral analgesics, the Medical Outcomes Study Health Survey Short Form-36 Item score, and the occurrence of adverse effects. The study results will be analyzed using intention-to-treat and per-protocol analyses. Primary and secondary outcomes will be evaluated between the mono and combined treatment groups. Subgroup analyses will be conducted based on the initial ailment, age, and baseline pain intensity. The safety of the treatment will be assessed by monitoring adverse events, which will be compared between the two groups.

**Discussion:**

This study protocol describes a randomized, controlled clinical trial to determine the efficacy and safety of mono and combination therapies in patients with pudendal neuralgia. The study results will provide valuable information on the potential benefits of this combination therapy and contribute to the development of more effective and safer treatments for patients with pudendal neuralgia.

**Trial registration:**

Chinese Clinical Trial Registry (ChiCTR2200061800).

## Background

Pudendal neuralgia (PN), also called Alcock’s syndrome or pudendal nerve entrapment syndrome, is characterized by sensations of burning pain, numbness, or paranesthesia across the pudendal nerve (anywhere between the anus and the clitoris) [1]. PN has been attributed to several factors, including inflammation, compression of the pudendal nerve between the sacrotuberous and sacrospinous ligaments, or compression at the pudendal canal level, which are commonly associated with childbirth, trauma, surgical sequelae, or intense bicycling [2]. This condition is chronic and debilitating. Its prevalence ranges from 5 to 26% [3], but may be significantly higher compared with that described in the literature. Patients may feel embarrassed to seek medical advice, whereas the diagnosis of PN can be challenging for health professionals because of the lack of specialized training in this area [4].

Therapeutic approaches to PN include patient education, medication management, psychological and physical therapy, and consideration of procedural interventions, including nerve block, trigger point injections, and surgery [5, 6]. Tricyclic antidepressants (amitriptyline), serotonin-norepinephrine reuptake inhibitors (duloxetine), and antiepileptics (gabapentin) are used as initial monotherapy for PN [6]. The number of patients required to be treated to achieve 50% pain relief from neuropathic pain ranges from 4 to 10, and the inadequate response of neuropathic pain to drug therapy constitutes a highly unmet need [7]. Surgery is the last resort for patients who have been suffering from PN for longer than a year. The remarkable benefit of surgery is the duration of pain relief, which can range from long-term (commonly 4 years) to permanent [5]; however, surgery is invasive. Therefore, therapeutic nerve blocks must be performed prior to referral to surgery [5, 8].

Pudendal nerve block (PNB) is an essential diagnostic tool and treatment method for PN. PNB can significantly decrease pain scores for a short period of time; however, its effect significantly decreases over time [5, 6, 8]. Labat et al. [2] reported that only 13% of patients experienced pain relief, with up to 50% lasting for 90 days following PNB. Kastler et al. [9] found that 6 months post-PNB, the clinical efficacy was 25.2%. Neuromodulation is a commonly used treatment approach for chronic pelvic pain; however, traditional continuous radiofrequency may damage nerves and may be irreversible. Continuous radiofrequency (CRF) is a widely used method for managing conditions, such as zygomatic joint osteoarthritis, trigeminal neuralgia, and occipital neuralgia. CRF may relieve PN, but may cause bowel, bladder, and sexual dysfunction [10]. Pulsed radiofrequency (PRF) is an alternative approach to avoid irreversible damage, in which the temperature is set in a range of 42–50 °C. PRF is effective for radicular pain from spinal diseases, post-herpetic neuralgia, and occipital neuralgia [11]. Fang et al. [10] showed that pudendal nerve PRF combined with PNB provides longer-lasting pain relief and alleviates depression in patients compared with PNB. Ji et al. [12] found that PN was alleviated after 6 months in 88.9% of the patients who received ultrasound-guided high-voltage long-duration PRF. At long-term follow-up (ranging from 2.3 years to 8.8 years), Krijnen et al. found that 89% of patients who received repeated PRF with a median interval duration of 3 months between two sessions described their condition as “(very) much better” [13]. No difference was observed between PNB and PRF immediately after the procedure, although PRF provided significant improvement in pain for 2 weeks to 3 months [12, 14].

Chronic pain is associated with the sympathetic nervous system, which may be treated with sympathetic nerve blocks. Ganglion impar is the terminal solitary ganglion of the bilateral paravertebral sympathetic chains that transmits pelvic and perineal nociceptive messages to the central nervous system. It primarily innervates the perineum, distal rectum, perianal, distal urethra, scrotum, and distal 1/3 of the vagina. Ganglion impar block (GIB) was first used in 1990 to alleviate pelvic cancer pain, and it is frequently targeted for the treatment of perineal and pelvic pain. Currently, GIB is widely used for treating chronic perineal pain and chronic coccygodynia [15–17]. Thus, ganglion impar, acting as vector of nociceptive messages between the visceral and central nervous systems, represents another therapeutic target in PN.

Ultrasound-guided PRF of the pudendal nerve combined with or without GIB is used to treat PN; however, a randomized controlled trial focused on whether pudendal nerve pulsed radiofrequency combined with ganglion impar block is more effective than pudendal nerve pulsed radiofrequency is lacking. Hence, we hypothesize that combined therapy (pudendal nerve pulsed radiofrequency + ganglion impar block) is more effective compared with monotherapy (pudendal nerve pulsed radiofrequency) for long-term improvement of PN.

## Methods

### Study design

This is a multicenter prospective randomized, controlled trial with 1:1 allocation (Fig. 1). It has been registered at www.ChiCTR.org (ChiCTR2200061800). Ethical approval was granted by the Medical Ethics Committee of West China Hospital, Sichuan University. Written informed consent will be obtained from patients or their legal representatives by the designated attending physicians after explaining the trial to patients.

**Fig. 1 Fig1:**
[figure not shown]
Consolidated Standards of Reporting Trial diagram for this trial. VAS, visual analog score; SAS, Self-Rating Anxiety Scale; SDS, Self-Rating Depression Scale; SF-36, Medical Outcomes Study Health Survey Short Form-36 Item (SF-36)

### Patients

The inclusion criteria for the study are as follows: (1) patients present with four essential clinical criteria for the diagnosis of PN based on the following Nantes criteria: (a) pain in the territory of the pudendal nerve (from the anus to the penis or clitoris); (b) pain is predominantly experienced while sitting; (c) pain does not typically disrupt sleep at night; (d) no objective sensory deficiency; (2) receiving analgesic medication for at least 2 weeks, but still has a VAS ≥ 4; (3) a VAS score decrease by more than 50% of the baseline after diagnostic PNB; (4) age 18–85 years.

The exclusion criteria for the study are as follows: (1) involved in other clinical trials within the last 3 months; (2) pregnant or plan to become pregnant; (3) heart disease; (4) nerve injury/central nervous system injury; (5) contraindications to injection with lidocaine, ropivacaine, mecobalamin, diprospan, or iodinated contrast medium; (6) active or recurrent urethral infection (more than five times in the last 12 months); (7) coagulation disorder or receiving anticoagulants; (8) received nerve block or PRF previously; and (9) refusal to participate in the trial.

### Randomization, concealment, and blinding

Randomly assigned sequences will be generated using SPSS 22.0 (IBM SPSS STATISTICS 22.0) by an independent research assistant, and the results will be sealed in an opaque envelope based on the chief investigator’s instructions. Eligible participants will be randomly assigned to the mono or combined groups at a 1:1 ratio. The allocation will not be revealed until all end point events have been evaluated for the last patient, or severe adverse effects have occurred. The patients and the attending physicians who conduct the treatments will not be blinded to the assigned treatment; however, the outcome assessors and statisticians will be blinded to the group assignments.

### Intervention

The designated attending physicians will conduct the PNB after admission, and evaluate the treatment effect 2 h after PNB. If the diagnostic PNB is positive (VAS score decreases by 50%), the patients will receive an allocation based on a random sequence by the chief investigator. The pudendal nerve PRF and GIB will also be conducted by the designated attending physicians at each center.

The combined group will receive pudendal nerve PRF and GIB. The interval between PNB and PRF will be 1 day to 3 days, and that between PRF and GIB will be 3 days to 5 days (Fig. 2). The mono group will only receive pudendal nerve PRF. Permissible interventions during the RCT will include relevant concomitant care, such as pelvic floor physical treatment, pelvic floor magnetic stimulation, and transcranial magnetic stimulation. If the pain improvement is less than 30% or the VAS score is greater than four, remedial analgesia will be administered, such as pregabalin, oxycodone, and acetaminophen tablets.

**Fig. 2 Fig2:**
[figure not shown]
The study treatment schedule

All patients will be evaluated in person one day after the completion of therapy. Furthermore, patients will use an electronic device to answer a questionnaire on VAS, SAS, SDS, and SF-36 at the time of each visit. The follow-up evaluation in person or online will be conducted by outcome assessors, who will be blinded to allocation. The scores and data collection date will be recorded on the electronic device.

### PNB

The patients will be in a prone position. First, an ultrasound transducer will be positioned at a transverse plane to visualize the ischium forming the lateral border of the sciatic notch. When the probe is moved in the cephalad–caudal direction, the length of the ischium gradually increases, with the widest point at the level of the ischial spine. The ischial spine will be identified by visualizing the internal pudendal artery again. Thereafter, a local anesthesia compound (2% lidocaine 1.5 ml + 1% ropivacaine 1.5 ml + 0.9% NaCl 2 ml) will be administered to the medial aspect of the internal pudendal artery (Fig. 3).

**Fig. 3 Fig3:**
[figure not shown]
Pudendal nerve block or PRF treatment. IS, ischial spine

### Pudendal nerve PRF

The patients will be placed in a prone position. Under ultrasound guidance, the puncture needle will be inserted near the pudendal nerve (Fig. 3). After connecting the electrode and PRF needle, sensory stimulation at a frequency of 50 Hz, pulse width of 1 ms, and voltage of 0.3–0.5 V will be administered to produce paresthesia in the innervation of the pudendal nerve. PRF will be administered at 42℃ for 480 s. Thereafter, a 5-ml nerve nutrition compound (2 ml of 2% lidocaine + 1 ml of 0.5 mg mecobalamin + 1 ml diprospan + 1 ml of 0.9% NaCl) will be injected.

### GIB

The patients will be placed in a prone position, and the sacrococcygeal junction will be identified using the CT-guided frontal and lateral views. When the needle pierces through the sacrococcygeal ligament under CT guidance (Fig. 4), a loss of resistance will occur. The position of the needle tip will be confirmed by injecting a contrast medium. Subsequently, a local anesthesia compound (1.5 ml of 2% lidocaine + 1.5 ml of 1% ropivacaine + 1 ml diprospan + 1 ml of 0.9% NaCl) will be administered to block the ganglion impar.

**Fig. 4 Fig4:**
[figure not shown]
CT-guided GIB

### Outcomes

The patient baseline characteristics will be documented at enrollment. The primary and secondary outcomes will be measured at 1 day (T1), 1 week (T2), 2 weeks (T3), 4 weeks (T4), 8 weeks (T5), 12 weeks (T6), and 24 weeks (T7) after the completion of treatment (Fig. 5). The collection of post-discharge outcomes will be performed by telephone interview or face-to-face when patients visit the clinic.

**Fig. 5 Fig5:**
[figure not shown]
Schedule of enrollment, intervention, and assessments. VAS, Visual Analog Scale; SAS, Self-Rating Anxiety Scale; SDS, Self-Rating Depression Scale; SF-36, Medical Outcomes Study Health Survey Short Form-36 Item (SF-36)

### Baseline characteristics

The following characteristics will be collected, including demographic characteristics (e.g., initial ailment, sex, age, parity, and history of vaginal delivery), medical history, duration of pain, and baseline score of VAS, SAS, SDS, and SF-36 scores.

### Primary outcome

The primary outcome will be the VAS score at T1, T2, T3, T4, T5, T6, and T7. The VAS score is a scale consisting of a line, usually 100 mm in length, from “no pain” (score of 0) to “worst imaginable pain” (score of 100).

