### Statistical analysis

Statistical analysis will be performed using SPSS 22.0 (IBM SPSS STATISTICS 22.0) according to the intention-to-treat and per-protocol analyses. The per-protocol set is defined as all patients who have undergone randomization and have received all treatment, except for those who dropped out because of poor efficacy. The Kolmogorov–Smirnov test will be used to evaluate the normality of the data distribution, and Levene’s test will be used to determine the homogeneity of variance. Continuous data will be represented as the mean with SD or median with the interquartile range based on its distribution. The categorical variable will be represented by counts and percentages. The difference between groups will be analyzed by a one-way analysis of variance, Mann–Whitney *U* test, chi-square, or Fisher’s exact tests as appropriate based on the type of variable. Generalized estimating equation analysis will be used for repeated measurement data. Missing data (e.g., loss to follow-up, death, withdrawal) will be updated using the multiple-imputation approach. A two-sided *P* value of 0.05 will be considered statistically significant.

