### Sample size

According to a previous study, the VAS score was 3.6 ± 1.9 after 1 month of PRF [10]. We assumed that the pudendal nerve PRF with GIB will decrease the VAS score by 30% with a total two-sided type I error rate of 0.05 and a 20% withdrawal rate. A total of 84 patients will be enrolled to achieve a statistical power of 80%.

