## Discussion

A prospective, randomized, controlled study will be conducted to evaluate the efficacy and safety of pudendal nerve PRF with GIB in PN.

Ultrasound-guided pudendal nerve PRF and CT-guided GIB have been widely used to treat chronic pain. To date, some retrospective studies, case reports, and case series on the efficacy of PRF or GIB in PN have been reported [13–15, 17, 20–22]. However, the ultrasound-guided PRF of the pudendal nerve combined with GIB is used in PN, but randomized controlled trials are lacking. In the above studies, the PRF parameters were set as follows: temperature ranging from 42 ℃ to 45 ℃ with a duration from 120 to 900 s. Although the high-voltage long-duration PRF mode shows better improvement in PN [12], based on our clinical experience and to avoid discomfort, PRF will be administered at 42 ℃ for 480 s in our study. Our primary outcome will be the efficacy of PRF combined with GIB for the long-term improvement of PN. At long-term follow-up (ranging from 2.3 years to 8.8 years), Krijnen et al. [13] found that most patients received repeated PRF therapy every 2 to 6 months. Thus, the follow-up will last for 24 weeks in our study.

Nevertheless, our study will have several limitations. First, the memory effect is an important mechanism in the development of chronic pain, and nerve block or PRF will be repeatedly implemented with an interval from a few days to weeks [23]. However, the patients in this study will receive only one pudendal nerve PR. Second, the success of pudendal PRF may be affected by the anatomical level of nerve injury. Interligamentous pudendal nerve entrapment patients experience more benefits than those having pudendal nerve entrapment in the endopelvic portion [8].

Overall, our study results will provide valuable information on the potential benefits of this combination therapy and contribute to the development of more effective and safe treatments for PN patients.

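### VAS at seven unranked visits is primary and no single test is named, so the overall 5% error rate is not guaranteed and the 1-month planning basis does not match the long-term question

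*Protocol article*

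**What the plan says.** All references are to the Protocol article.

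- **Primary outcome:** "The primary outcome will be the VAS score at T1, T2, T3, T4, T5, T6, and T7". The Outcomes section gives the timing: T1 is 1 day and T2 is 1 week, followed by "2 weeks (T3), 4 weeks (T4), 8 weeks (T5), 12 weeks (T6), and 24 weeks (T7) after the completion of treatment". No visit is put ahead of another.
- **Abstract, Methods:** "The primary outcome will be a change in pain intensity measured using the visual analog scale", with no time point.
- **Background:** the hypothesis is that the combination "is more effective compared with monotherapy (pudendal nerve pulsed radiofrequency) for long-term improvement of PN".
- **Discussion:** "Our primary outcome will be the efficacy of PRF combined with GIB for the long-term improvement of PN". Follow-up length is justified in the same place: "Thus, the follow-up will last for 24 weeks in our study".
- **Sample size:** the planning figure is that "the VAS score was 3.6 ± 1.9 after 1 month of PRF". A 30% reduction, 80% power, 20% withdrawal and a two-sided type I error described as a total of 0.05 lead to 84 patients.
- **Statistical analysis:** simple between-group tests are chosen by type of variable, GEE is assigned to repeated measurements, and a two-sided P "value of 0.05 will be considered statistically significant". No visit, GEE contrast or success criterion is identified as primary.

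**The concern.** A confirmatory trial needs one result, fixed in advance, that decides whether the hypothesis is supported. Here the outcome section gives seven candidates equal standing, the Discussion points to the late ones, and the power statement points to about T4.

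The visits are not interchangeable. T1 falls one day after the last procedure, which in the combined group is the ganglion impar block itself. A difference at T1 says little about long-term improvement, yet it has the same primary status as the 24-week result. As the text stands, a report could present any visit, or any of several GEE contrasts, as the primary finding, and a reader could not tell from the article whether that choice was made in advance. The overall 5% error rate and the 80% power would then not clearly belong to the claim being made.

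**Working it through.** **1. The places side by side**

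| Section | What it fixes | Time point |
|---|---|---|
| Primary outcome | VAS is primary | all of T1 to T7 |
| Abstract, Methods | change in VAS is primary | none given |
| Discussion | long-term improvement is primary | late, not named; follow-up ends at 24 weeks |
| Background | hypothesis on long-term improvement | late, not named |
| Sample size | planning mean and SD | 1 month, about T4 |
| Statistical analysis | tests and threshold | none given |

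Three of these cannot all describe one primary test: seven equal visits, a long-term effect, and a 1-month planning basis.

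**2. The plan's own figure**

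Inputs from Sample size: mean 3.6, SD 1.9, 30% reduction (read as 0.30 × 3.6 = 1.08 points), two-sided 0.05, power 80%, withdrawal 20%, 1:1 allocation.

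n per arm = 2 × (1.960 + 0.842)² × 1.9² / 1.08² = 48.6, so 49 per arm or 98 evaluable. With withdrawal, 49 / 0.80 = 61.25, so 62 per arm or 124 enrolled.

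The stated 84 is not reproduced. That is a separate matter and this point does not rest on it. What matters here is that the inputs describe one comparison at one early time. The article gives no 24-week mean or SD, so no sample size or power for 24 weeks can be computed from it.

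**3. Error rate if visits were tested separately and any one counted**

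This is a conditional calculation; the article states neither rule. With seven independent tests it is 1 − 0.95⁷ = 0.302. The visits come from the same patients, so positive correlation is expected. The article gives none, so a range is assumed. Simulating seven correlated z-statistics under no effect (500,000 replicates) gives the chance that at least one |z| exceeds 1.96:

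| Correlation | Equal between all visits | AR(1) |
|---|---|---|
| 0.3 | 0.271 | not run |
| 0.5 | 0.230 | 0.268 |
| 0.7 | 0.178 | 0.225 |
| 0.8 | 0.148 | 0.193 |
| 0.9 | 0.114 | 0.147 |

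**4. Error rate for one prespecified GEE contrast**

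One test at two-sided 0.05 has a nominal error rate of 0.05, whether the contrast is the difference at one visit or one overall group effect.

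**5. What it would take to keep all seven visits primary**

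If any visit may win, the Bonferroni level is 0.05 / 7 = 0.00714, with critical value 2.690. Applying the 1-month inputs to every visit (an assumption), n per arm = 2 × (2.690 + 0.842)² × 1.9² / 1.08² = 77.2, so 78 per arm. With withdrawal, 78 / 0.80 = 97.5, so 98 per arm or 196 enrolled, against 84 planned.

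**The case against.** A reader might infer that every visit is tested at 0.05 and that the trial's false-positive rate is therefore inflated, perhaps to 30%. The article does not support that. VAS at T1 to T7 is repeated measurement data, which the Statistical analysis section assigns to GEE. The natural reading is that the simple tests serve baseline and single-occasion variables. One GEE group effect would hold the nominal level. The Sample size section also speaks of a total error rate, which suggests an overall 5% was intended rather than 5% per visit. The 30% figure needs independence across visits in the same patients, which is implausible.

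A reader might also count four or more rival definitions of the primary outcome. That goes too far. The Sample size section borrows planning values and the Background states a hypothesis; neither defines an outcome. The abstract's change in VAS is compatible with VAS at follow-up visits, since baseline VAS is collected.

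Finally, the mechanics of contrasts and multiplicity are commonly left to a statistical analysis plan, which is not shown.

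These arguments stand against the stronger claims but leave the core intact. GEE over seven visits can yield an overall effect, a group-by-time interaction or seven visit contrasts, and the article chooses none. Stating a total of 0.05 does not by itself control it. A separate analysis plan could name a contrast, but the article's text would still hold a seven-visit primary outcome, a long-term primary outcome and a 1-month planning basis.

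**Conclusion.** The point holds in this form: the primary outcome is seven unranked visits in one section and long-term improvement in another, the trial is sized on 1-month data, and no primary visit, GEE contrast or success rule is designated. The overall type I error of 0.05 is therefore not guaranteed. The documents do not show that it is exceeded.

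The size depends on how the gap is filled: about 5% with one prespecified GEE contrast, and about 11% to 30% if visits were tested separately and any one counted. The upper range rests on those two unstated rules and on assumed correlations from 0.9 (equal between visits) down to independence. The case for correction rests on the undesignated primary test, not on the simulated rates. It should be corrected before unblinding because it concerns the trial's main claim.

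**What to change.** Before unblinding, and without sight of outcome data by group, name one primary test from the planned GEE at two-sided 0.05.

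- **Difference at T7 (24 weeks).** This matches the long-term hypothesis. The Sample size section must then say that its 1-month inputs are only a proxy, because no 24-week mean or SD is given.
- **Difference at T4, or one overall group effect across visits.** T4 matches the planning data; the overall effect is one test from the planned model. With either, the long-term claim must be reworded as secondary.

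Make all other visits and the simple group tests secondary, or test them in a fixed sequence or with Holm. Align the Abstract, Primary outcome, Statistical analysis, Sample size and Discussion to the one definition. Trial status says that recruitment began on 1 May 2023 and was expected to finish by December 2023, so record the date of the decision and that it was made blind to results by group.

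The cost is wording, with no new data. Other visits can no longer be claimed as primary, and with T7 the stated 80% power is no longer directly supported.

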### Data collection and management

#### Data collection

Before recruitment, all investigators will be invited to evaluate the design and explore the feasibility of the intervention. Standard operating procedures will be established in detail. All investigators will be trained on the grading rules of scales and matters that need attention to guarantee the quality of the trial. The procedures will be carried out by designated pain physicians and follow-up will be performed by a trained research assistant.

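### The primary VAS is defined on 0-100, but the entry threshold, the absolute rescue threshold and the planning values only make sense on 0-10

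*Protocol article*

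**What the plan says.** All of the relevant text is in the Methods of the protocol article.

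- **Primary outcome** defines the score on a line "usually 100 mm in length, from “no pain” (score of 0) to “worst imaginable pain” (score of 100". No other section gives a range for it.
- **Patients**, inclusion criterion 2, admits a patient "receiving analgesic medication for at least 2 weeks, but still has a VAS ≥ 4".
- **Intervention** sets the rescue rule: "If the pain improvement is less than 30% or the VAS score is greater than four, remedial analgesia will be administered". The first condition is relative and the second is absolute.
- **Sample size** takes from an earlier study that "the VAS score was 3.6 ± 1.9 after 1 month of PRF", and continues: "We assumed that the pudendal nerve PRF with GIB will decrease the VAS score by 30"%.

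None of the last three carries a unit, and no conversion is given anywhere in the article. Two further sections bear on the consequences. Secondary outcomes lists use of remedial analgesics at every visit from T1 to T7. Intervention also says that "patients will use an electronic device to answer a questionnaire on VAS, SAS, SDS, and SF-36 at the time of each visit".

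**The concern.** The article declares one scale for its primary outcome and uses another wherever it puts a number on that outcome. A VAS of 4 on a 0-100 score is almost no pain, yet it is the entry threshold for patients with a condition that the Background describes as chronic and debilitating. On the declared scale, the entry criterion would exclude almost nobody in pain, and the absolute rescue condition would be met by almost anyone with residual pain.

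Two operational rules depend on the figure: who enters, and who receives rescue analgesia. The second feeds an endpoint, because remedial analgesic use is itself a secondary outcome. The trial is multicenter, and the article describes data collection by electronic device, online, by telephone and face to face. A score given as a number, rather than as a mark on a line, needs a stated range that is the same in every mode.

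**Working it through.** **Inputs.** Declared range 0 to 100 (Primary outcome). Entry threshold 4 (Patients). Rescue threshold 4 or relief below 30% (Intervention). Planning mean 3.6, SD 1.9 and a 30% reduction (Sample size).

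**Step 1. Each figure as a share of the range.** The assumed difference is 0.30 × 3.6 = 1.08.

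| Figure as printed | Share of 0-100 | Share of 0-10 |
|---|---|---|
| Entry and rescue threshold, 4 | 4/100 = 4% | 4/10 = 40% |
| Planning mean, 3.6 | 3.6% | 36% |
| Planning SD, 1.9 | 1.9% | 19% |
| Assumed difference, 1.08 | 1.08% | 10.8% |

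The 0-10 column describes a plausible pain population. The 0-100 column does not: patients would be close to pain-free after PRF, with hardly any spread between them.

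**Step 2. What the literal rescue rule would do.** Take a patient at 40 on the 0-100 score, which is the evident entry level, whose pain then falls by 50% to 20. The relative condition is not met, because 50% is not below 30%. The absolute condition is met, because 20 > 4. To escape it, this patient would have to fall from 40 to 4, that is by 36/40 = 90%. On a 0-10 score the same patient goes from 4 to 2, and since 2 is not above 4, no rescue is due.

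**Step 3. Does the unit affect the sample size?** The standardised difference is 1.08/1.9 = 0.568 on 0-10. Multiplying everything by 10 gives 10.8/19 = 0.568. The normal-approximation formula for two means, with 80% power and the stated "total two-sided type I error rate of 0.05 and a 20% withdrawal rate", is

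n per arm = 2 × (1.960 + 0.842)² × (SD/difference)²

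- 0-10: 2 × 7.85 × (1.9/1.08)² = 48.6, so 49 per arm.
- 0-100: 2 × 7.85 × (19/10.8)² = 48.6, so 49 per arm.

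The unit therefore makes no difference. Allowing for withdrawal, 49/0.8 = 61.25, so 62 per arm and 124 in total. The printed total of 84 is not reproduced, but the unit problem does not explain that. Mixing the scales would give 4,859 per arm (difference 1.08, SD 19) or 1 per arm (difference 10.8, SD 1.9). The shortfall is a separate matter and adds no weight to this point.

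**Step 4. What else is free of the unit.** The 50% fall required after the diagnostic block, the 30% condition of the rescue rule and the assumed 30% reduction are all ratios. Between-group P values for the VAS do not change when every score is multiplied by the same constant.

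**The case against.** The strongest reply is that nobody will be misled. A 100 mm line is a 10 cm line, so 4 and 3.6 are positions on that same line in centimetres, and what is missing is a unit rather than a coherent outcome. The definition hedges with the word usually and reads like a textbook description of the instrument. The article also says "All investigators will be trained on the grading rules of scales" and promises detailed operating procedures. The full protocol, version 3.0, is not shown and may state the unit. The value 3.6 ± 1.9 comes from an earlier study and may simply be quoted on that study's scale.

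Much of this stands. Staff will probably apply 4 as 4 out of 10, nothing shows that the electronic device is set to a conflicting range, and the planning values have no operational effect. The two thresholds are therefore the part that matters.

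Three things do not fall away. The hedge applies to the length of the line, while the anchors of 0 and 100 are stated without one. A condensed article may leave detail out, but this is not an omission: one scale is declared and another is used. And an eligibility criterion and a rescue trigger should not depend on readers silently correcting the definition of the primary outcome.

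**Conclusion.** The point holds as an internal inconsistency of units in the article as written. Two decision thresholds are printed at 4% of the declared range where 40% is evidently meant, and the planning values show the same tenfold mismatch. The consequence is minor: it touches entry and the absolute rescue condition, and through rescue one secondary outcome. It does not touch the sample size, the relative rules or the between-group P values, and it is no threat to the design.

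The conclusion rests on one inference. No unit is printed beside 4, four or 3.6 ± 1.9, so the 0-10 reading is drawn from plausibility, although no other reading fits. It does not assume that any patient has been enrolled, rescued or scored on the wrong scale.

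**What to change.** Use one scale throughout, in either of two ways:

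1. In Primary outcome, define the score as 0 to 10, measured in centimetres on the 100 mm line. The thresholds and planning values can then stay as printed, with the unit added.
2. Keep 0 to 100, and change entry to at least 40, the absolute rescue condition to above 40, and the planning values to 36 ± 19 with an assumed difference of 10.8.

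The first needs fewer edits. Under either, confirm that the electronic questionnaire and the telephone interview use the same range. Recruitment was due to finish in December 2023, so scores already collected should be checked for a common unit and the results reported with that unit stated.

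The cost is a few words in the protocol and one check of a range setting. Design, sample size and analysis stay as they are.
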